### Data management

3.11

Any decisions about outputs and decisions from this trial should be ratified by the trial Management Committee ([name]) and each of the named investigators shall be eligible to have authorship. All data management should be overseen for quality by our management committee. Data entry and coding of the deidentified data will be conducted by trained staff and we will use range checks for data values.

### Statistical analysis

3.12

For participants in the 2 groups, the intervention and control, medication adherence will be measured and documented based on the BASSIS self-report at baseline, 2, 4, and 6 months. For determining effect of each predictor variable and modifying the effect of confounding, we will use ordinary logistics regression and multinomial logistics regression models. To evaluate quantitative variables at different time points, if the variables have a Gaussian distribution, the repeated ANOVA measure, and otherwise the Friedman test, will be used. Cochrane test will be used to evaluate and compare medication adherence across different time points. *P*-values less than .05 will be considered as statistically significant. All statistical analyzes will be performed using the Statistical Package for the Social Sciences, version 23, IBM. The electronic data file is stored on secure data servers and its hard copy version will be stored in a locked file at MUMS.

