### Outcomes measure

3.5

Study outcomes will be evaluated in accordance with Table 1. Primary and secondary outcomes are measured at baseline, and at 2-months, 4-months, and 6-months after baseline. For ethical reasons, if the intervention is found to be effective, all groups will have access to IVRS at the end of the intervention. Primary outcome will be immunosuppressive medication adherence that is evaluated based on a self-report in both groups during the follow-up period. The secondary outcomes include transplant knowledge, HRQoL, and rehospitalization rate.

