Patients’ transplant knowledge treatment process will be measured using the kidney transplant understanding tool (K-TUT).^[29]^ This questionnaire was first translated to Persian by 2 researchers (forward) and then back-translated by 1 individual (backward). Questionnaire's content validity was checked through 1 round of a Delphi session with the participation of 4 nephrologists and 4 coordinator nurses. To assess content validity quantitatively, the content validity index (CVI) and content validity ratio (CVR) indices were used. CVI was computed as the number of experts giving a rating 3 or 4 to the relevancy of each item, divided by the total number of experts. In order to determine CVR, the experts were asked to examine each item based on a 3-part spectrum: it is “necessary,” “useful,” and “not necessary,” Then the responses were evaluated according to the formula (the number of specialists selecting the “necessary” option divided by the total number of the specialists). Items with CVI values less than 0.78 were deleted. The questionnaire reliability was checked through test-retest reliability analysis. The questionnaire was given to 25 recipients. After a week they were asked again to answer the questions, and Pearson Correlation Coefficient was calculated for patient's transplant knowledge scores. This coefficient was 0.72, indicating the questionnaire acceptable level of reliability. The final questionnaire contained 9 true/false and 13 multiple choice questions (more than 1 correct answer). One score was given to each correct answer. The maximum knowledge score was 57. Higher knowledge scores indicated more KT knowledge.

In order to assess the health-related quality of life, the 12-item short form survey, second version (SF-12V2) questionnaire was administered. This questionnaire was validated by Montazeri et al for a group of Iranian patients.^[36]^ This 12-item questionnaire evaluates a general understanding of your health, physical performance, physical health, emotional problems, physical pain, social function, vitality and vital energy, and mental health. The maximum quality of life score is 48. A score greater than 37 indicates a good quality of life, a score between 25 and 36 indicates intermediate quality of life, and a score less than 24 indicates poor quality of life.

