## Results

4

We have complete preliminary qualitative and expert opinion studies that provide educational content, profile information, and intervention design. Recruitment of participants has not been completed and results will be published in 2019. The IVRS is potentially useful to help KT recipients improve self-management outcomes. Using IVRS intervention will make significant differences between BAASIS, SF-12V2, K-TUT scores, when comparing these at baseline and at the end of study.

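### No adjusted between-group model is named for the quality-of-life and transplant-knowledge scores: the named regressions need categorical outcomes, and the tests given to scores are worded as time comparisons

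*Protocol article*

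**What the plan says.** The Outcomes measure section (3.5) makes adherence the primary outcome and adds: "The secondary outcomes include transplant knowledge, HRQoL, and rehospitalization rate". Outcomes are measured at baseline and at 2, 4 and 6 months.

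The Data collection tools section (3.10) defines two numeric scores. For knowledge, "The maximum knowledge score was 57", and no cut-point is given. For quality of life, "The maximum quality of life score is 48", followed by an interpretation in bands: "A score greater than 37 indicates a good quality of life, a score between 25 and 36 indicates intermediate quality of life", with poor below 24. BAASIS adherence is reduced to adherent or non-adherent.

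The Statistical analysis section (3.12) gives a purpose, "For determining effect of each predictor variable and modifying the effect of confounding", and the models for it: "we will use ordinary logistics regression and multinomial logistics regression models". No outcome is assigned to either model. The next sentence covers quantitative variables at different time points: "if the variables have a Gaussian distribution, the repeated ANOVA measure, and otherwise the Friedman test, will be used".

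The Results section (4) states the expectation: "Using IVRS intervention will make significant differences between BAASIS, SF-12V2, K-TUT scores".

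**The concern.** The models meant for effects and confounding do not accept the SF-12V2 or knowledge score as an outcome, and the methods that do accept a score are described as comparisons over time. The trial's question about these outcomes is whether the intervention arm does better than usual care, and no stated method answers it on the score with adjustment.

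Two things are at stake. First, an analyst following the text could report a change over time, perhaps separately by arm, in place of a treatment effect. A significant change in one arm and a non-significant change in the other is not a test of the difference between arms. Second, an analyst wanting an adjusted effect from the named models would have to cut the score. The SF-12V2 has three published bands to hand, and knowledge has no cut-point, so one would have to be invented. Cutting loses power and leaves room for choosing the cut after seeing the data.

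**Working it through.** **Step 1: match each method to each outcome.**

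| Method named in 3.12 | Accepts a numeric outcome? | Group term? | Covariates? |
|---|---|---|---|
| Logistic regression | No, two categories (or ordered categories if *ordinary* means *ordinal*) | Possible | Yes |
| Multinomial logistic regression | No, unordered categories | Possible | Yes |
| Repeated-measures ANOVA | Yes | Possible, not stated | Possible, not stated |
| Friedman test | Yes (ranks) | No | No |

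No row gives a stated adjusted between-group effect on a score. If the scores are not Gaussian, the plan moves to Friedman and even the possibility of a group term goes.

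**Step 2: what cutting the SF-12V2 would cost, if it were done.** The article gives no SF-12V2 effect, mean or SD, so these are assumptions.

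The one planning figure is 40 per group at 90% power and two-sided 0.05, for medication adherence. It cannot be reproduced, because the article gives no rates, difference or SD. Read as a two-mean comparison it implies

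d = (z for 0.975 + z for 0.90) × √(2/n) = (1.960 + 1.282) × √(2/40) = 0.725 SD.

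This serves only as a convenient effect size. A difference of 0.5 SD at the recruited 60 per group was also tried.

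Simulation: rounded normal totals limited to 0–48, control means 27, 30.5 and 34, SDs 6 and 8, 2,000 trials per setting. Bands were cut at 24.5 and 36.5, because totals of exactly 24 and 37 fall in no stated band. Three tests were compared: a t-test on the score; the 2-df likelihood-ratio test on three bands (a multinomial model with group as the only predictor); and a 1-df rank test on the ordered bands (close to proportional odds).

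| Setting | Score | Multinomial, 3 bands | Ordered bands | Score minus multinomial |
|---|---|---|---|---|
| 40 per group, 0.725 SD | 88–90% | 70–73% | 77–81% | 15–18 points |
| 60 per group, 0.5 SD | 76–79% | 53–60% | 63–70% | 18–25 points |

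Two examples: at 40 per group, mean 27, SD 8, 0.885 − 0.731 = 0.154; at 60 per group, mean 30.5, SD 6, 0.790 − 0.545 = 0.245.

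A separate run over means 26–34 and SDs 6–10 gave a loss of 13 to 22 points, with null rejection rates of 0.055 to 0.059 for all three tests (checked at mean 30, SD 8). Together these give roughly 13 to 25 points. The loss is smaller where the score analysis is close to full power: at 60 per group and 0.725 SD it is 8 to 11 points (for example 0.976 − 0.897 = 0.079 and 0.965 − 0.854 = 0.111).

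The simulation is unadjusted and uses one visit. It shows the cost of cutting the score, not the exact power of this four-visit design.

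**The case against.** The strongest reply is that the article never says quality of life will be banded for analysis. The bands in 3.10 interpret a score, the regression sentence in 3.12 follows directly on the one about adherence, and the sentence after it keeps quantitative variables on their own scale. The Results section also speaks of scores. This stands. A reader might infer that the plan discards the SF-12V2 score and its band order and so loses power, but the documents do not support that.

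A reader might also infer that the multinomial model has no use here and should be deleted. That is not established either. BAASIS distinguishes missed doses, consecutive missed doses, timing deviations and dose reductions, and a type-of-non-adherence outcome could be nominal. The article does not state that use, but it does not exclude it.

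The word *ordinary* may be a slip for *ordinal*. If so, an order-preserving model is already named, and the complaint about lost band order weakens. The scores would still have no regression on their own scale.

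Finally, this is a condensed article, and mapping outcomes to models is often left to an analysis plan. That limits the point, but does not remove it. The article does choose methods for effects and for scores, and the stated choice for scores falls back on a test that can hold neither group nor covariates.

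**Conclusion.** The point holds in limited form. As written, 3.12 provides no adjusted between-group estimate for the SF-12V2 or knowledge score unless the score is first categorised. This follows from the text and needs no assumed figures.

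The power loss of roughly 13 to 25 points is conditional on two things: that the SF-12V2 would be analysed as three bands in a multinomial model, which is nowhere stated, and on the assumed means, SDs and effects. Both scores are secondary outcomes with no stated power, so no planning figure is missed. The point does not touch the binary classification of the primary outcome, for which logistic regression is suitable. The change is worth making because a better method than the stated one is available at almost no cost.

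**What to change.** In 3.12, state that the between-group effect on the SF-12V2 total and on the knowledge score will be estimated with a linear mixed model on the score. Include group, time, group-by-time interaction, baseline score, transplant-date stratum and the same confounders intended for the logistic models. Make this the treatment comparison for these outcomes, in place of the ANOVA or Friedman time-point tests.

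Keep binary logistic regression for adherent versus non-adherent. If the SF-12V2 bands are reported, analyse them with ordinal rather than multinomial regression, labelled supportive. Say which outcome each named model serves; if the multinomial model has a purpose, such as type of non-adherence, name it.

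The cost is a few sentences. No new data or patients are needed, and SPSS 23, the named software, fits both linear mixed and ordinal models. The small downside is that residuals must be checked and, if the bands are modelled, the proportional-odds assumption too.

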### Sample size

3.6

According to the study by Garcia et al,^[35]^ an study effect size based on 90% power and data with a 2-tailed *α* = 0.05, in medication adherence between the control and intervention groups, was estimated to be 40 patients in each group. Considering the 50% prop up rate during the study, our goal is to employ 60 patients in each group.

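### Knowledge and quality of life: a repeated-measures ANOVA that keeps baseline as one of four visits, with no baseline adjustment, is a weaker comparison of the arms than a baseline-adjusted one

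*Protocol article*

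**What the plan says.** The Outcomes measure section (3.5) sets the schedule: "Primary and secondary outcomes are measured at baseline, and at 2-months, 4-months, and 6-months after baseline". The secondary outcomes include transplant knowledge and health-related quality of life. Under Randomization (3.8) the assistant researcher collects the baseline questionnaire before the patient is allocated, so the intervention cannot affect the baseline score.

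The Statistical analysis section (3.12) gives one method for quantitative variables: "To evaluate quantitative variables at different time points, if the variables have a Gaussian distribution, the repeated ANOVA measure", with the Friedman test otherwise. It names no baseline covariate, change score or arm contrast for these outcomes. The regression models in the same section are logistic, which does not suit a score. The threshold is that P-"values less than .05 will be considered as statistically significant".

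The Sample size section (3.6) covers adherence only: "in medication adherence between the control and intervention groups, was estimated to be 40 patients in each group", "based on 90% power". No effect size, SD or between-visit correlation is given for K-TUT or SF-12V2.

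**The concern.** A repeated-measures ANOVA over baseline and months 2, 4 and 6 has a four-level time factor, and at one level the expected difference between randomised arms is zero. Two standard terms can compare the arms in that layout. The group main effect averages the zero baseline difference with three real ones, which dilutes the estimate. The group-by-visit interaction keeps the full difference in change, but spreads it over 3 df when the expected pattern is mostly one contrast, follow-up against baseline. Neither makes the best use of the baseline score, which predicts follow-up and could remove variance from the comparison.

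At stake are the size of the reported effect, if the main effect is used, and the chance of detecting a real effect on two named outcomes in a small trial.

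**Working it through.** **The plan's own figure.** The 40 per arm is for adherence and cannot be rebuilt, because no rates or effect size are stated. If 40 per arm at 90% power and two-sided 0.05 came from a comparison of two means, the implied effect would be (1.960 + 1.282) × √(2/40) = 0.725 SD. I use that only as an upper value. The enrolment goal of 60 is 40 × 1.5. If the stated 50% is a loss rate, 60 × 0.5 = 30 remain, so I also show 30 and 60 per arm.

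**Assumed inputs.** Unit SD, equal correlation r between all visits (compound symmetry), and a constant effect d at months 2, 4 and 6. The value of d is 0.4, 0.5 or 0.725, and r is 0.3, 0.5 or 0.72. The last is the one-week K-TUT retest coefficient in Data collection tools (3.10), not a correlation over months.

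**Size of the estimate**
- Group main effect over four visits: (0 + d + d + d)/4 = 0.75d. A 20,000-run simulation gave 0.751. If the effect instead rises linearly to d at month 6, it is (0 + 1/3 + 2/3 + 1)d/4 = 0.50d.
- Group-by-visit: its contrasts recover the full difference in change, so there is no shrinkage.

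**Power formulas, n per arm**
- A, four-visit group effect: effect 0.75d, variance (1 + 3r)/4.
- B, group-by-visit: the deviations of (0, d, d, d) from their mean have sum of squares (0.75² + 3 × 0.25²)d² = 0.75d². Noncentrality is (n/2)(0.75d²)/(1 − r), on 3 and 3(2n − 2) df.
- C, mean of months 2, 4 and 6 without baseline: effect d, variance (1 + 2r)/3.
- D, the same mean with baseline as covariate: effect d, variance (1 + 2r)/3 − r².

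For A, C and D the noncentrality is effect/√(2 × variance/n), referred to the noncentral t. With n = 40, d = 0.5, r = 0.5:
- A: variance 0.625, 0.375/√(0.03125) = 2.12.
- B: 20 × 0.1875/0.5 = 7.5.
- C: variance 0.667, 0.5/√(0.0333) = 2.74.
- D: variance 0.417, 0.5/√(0.0208) = 3.46.

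| n per arm | d | r | A | B | C | D |
|---|---|---|---|---|---|---|
| 40 | 0.5 | 0.3 | 67.1% | 46.2% | 85.6% | 91.2% |
| 40 | 0.5 | 0.5 | 55.4% | 61.5% | 77.2% | 92.8% |
| 40 | 0.5 | 0.72 | 46.2% | 87.5% | 68.8% | 98.2% |
| 40 | 0.725 | 0.3 | 93.6% | 80.7% | 99.2% | 99.8% |
| 40 | 0.725 | 0.5 | 85.9% | 92.6% | 97.5% | 99.9% |
| 30 | 0.4 | 0.72 | 25.1% | 53.9% | 39.3% | 80.1% |
| 60 | 0.4 | 0.72 | 45.0% | 86.3% | 67.3% | 97.9% |

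D is highest in every row. A against D loses between 6 points (d = 0.725, r = 0.3) and 55 points (30 per arm, d = 0.4, r = 0.72). At r = 0.72, B beats C, so dropping baseline without adjusting for it can be worse than keeping it as a level.

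**Baseline as covariate in the four-level model.** Given baseline, the four-visit mean is 0.75 times the post-baseline mean plus a known quantity. The estimate and its standard error both scale by 0.75, so the test and its power equal D. Only the reported group estimate stays on a 0.75 scale.

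**The case against.** A reader might infer that the plan shrinks the intervention effect to three quarters by design. The documents do not support that. Section 3.12 never says which ANOVA term compares the arms. The Results section expects the scores to differ between baseline and the end of the study, which points to change over time and so to group-by-visit, the term with no shrinkage. The explicit four-visit list in 3.12 is attached to adherence. That baseline is a level of time for the scores is the natural reading of 3.5 and 3.12 together, but it is not stated.

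It is also fair that no effect size or correlation is given for these outcomes, so the power figures rest on chosen inputs and the loss can be small. Only secondary outcomes are concerned. A full protocol or analysis plan, not shown, may fix the term and the role of baseline, and a condensed article may leave that detail to it.

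All of this stands and limits the point. It does not remove it. The article does name a method, and under the assumptions examined neither usual arm test from that method, without baseline adjustment, matches a baseline-adjusted comparison of the same data.

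**Conclusion.** The point holds conditionally, as an inexpensive improvement to the analysis of K-TUT and SF-12V2. If the group main effect over all four visits is used, the estimate is 0.75 of the mean post-baseline effect. This is exact whatever d and r are, given no expected baseline difference. If group-by-visit is used, the estimate is not diluted, and the cost is the 3-df test.

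The size of the power loss depends on assumed effects, correlations and compound symmetry. At 40 per arm and r = 0.5, the two tests have about 55% and 62% power against 93% when d = 0.5, and 86% and 93% against over 99% when d = 0.725. It does not follow that a real effect is likely to be missed in this trial. The primary adherence analysis and its sample size are not affected.

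**What to change.** In section 3.12, state for K-TUT and SF-12V2 that the repeated outcome is the score at months 2, 4 and 6, that the baseline score enters as a covariate, and that the arms are compared by one pre-specified 1-df contrast (the average over the three visits, or month 6), reported with a 95% CI. Do not simply drop baseline without adjusting for it. If the full protocol or analysis plan already says this, bring the article's sentence into line with it.

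The cost is wording only, with the same data and visits. The small downside is that a 1-df average is less sensitive than an omnibus test to an effect that reverses between visits.

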### Participants

3.3

KT recipients who will be referred to the center in July 2018 for follow up visits and caretaking are screened for eligibility. Eligible patients will be asked to provide consent with appropriate trail information and enough time to study and ask questions. Patients will be received 2 types of information related to the study:

(1)fully understandable oral information(2)2informed consent, in which the study design is described completely.

Informed consent has already been evaluated by the Ethics Committee of MUMS (IR.MUMS.fm.REC.1396.160). We ensure participants can withdraw from the study at any time without any commitment and no effect on their subsequent care. Eligible participants will be included after completing informed consent.

The inclusion criteria are as follows:

(1)KT recipients who have received a KT between 20 March 2012 and 20 March 2017,(2)having 18 years of age or more,(3)having acceptable graft function (do not need any types of dialysis),(4)having access to a mobile phone,(5)being able to read the informed consent information, and(6)willingness to participate.

The patients who are refused to participate in the study will be excluded. KT patients will be randomly assigned to the control (usual care) or intervention (usual care plus IVRS) groups. Usual care includes an educational booklet for KT and patient education provided by the nephrologists.

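### For the K-TUT and SF-12 scores, section 3.12 names only tests across visits and no comparison of IVRS with usual care, and its non-Gaussian fallback (Friedman) cannot contain a treatment factor

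*Protocol article*

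**What the plan says.** The hypothesis at the end of the Introduction is between arms: self-management should improve with IVRS relative to usual care alone. Section 3.5 lists transplant knowledge and health-related quality of life as secondary outcomes, measured at baseline and at 2, 4 and 6 months. Both are numeric scores under section 3.10. For K-TUT, "The maximum knowledge score was 57"; for SF-12 the maximum is 48.

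Section 3.12 gives one rule for such data, introduced as evaluation at different time points: "if the variables have a Gaussian distribution, the repeated ANOVA measure, and otherwise the Friedman test, will be used". The threshold is that "values less than .05 will be considered as statistically significant". No arm term is stated for the ANOVA, and no between-arm rank test is named for the other branch. Logistic and multinomial models are planned for predictor effects and confounding, but no outcome is assigned to them.

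Section 4 words the expected finding as a change over time: "Using IVRS intervention will make significant differences between BAASIS, SF-12V2, K-TUT scores, when comparing these at baseline and at the end of study". Section 3.3 describes what controls receive: "Usual care includes an educational booklet for KT and patient education provided by the nephrologists".

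**The concern.** The Friedman test ranks the visits within each patient and asks whether the visits differ. It has no place for a treatment factor: pooled, it ignores arm; run within one arm, it ignores the other. If the scores fail the distribution check, the named test cannot say whether IVRS did better than usual care. The ANOVA branch could answer that question with an arm-by-visit term, but the text does not mention one. If only its time effect is read, it has the same gap.

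Shared change is plausible here. Controls also receive education, and both arms are assessed on the same instruments four times, so usual-care learning or retest gain can raise scores in both. A significant visit effect could then be reported as the difference that section 4 anticipates, with no IVRS effect behind it. The reverse can also happen: if the arms move in opposite directions, a pooled visit test sees little.

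**Working it through.** **No figure to reproduce.** The document computes nothing for these outcomes. Its sample size (section 3.6: 40 per arm, 60 per arm recruited) is for medication adherence and serves here only as the pair of sizes to examine.

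**Inputs from the document.** Four visits (3.5); two arms, 1:1 (3.8); significance at .05 (3.12); 40 or 60 per arm (3.6).

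**Assumed, because the document does not give them.** Size of the shared change, 0.1 to 0.5 SD; within-patient correlation 0.5; normal data with an equal shift d at all three follow-ups in both arms; no IVRS effect. A linear trend and skewed (log-normal-type) errors are shown as variations.

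**Analytic check of the pooled Friedman test.** With k = 4 visits and N patients, the statistic is referred to chi-square on 3 df (5% critical value 7.81). Its approximate noncentrality is λ = [12N / (k(k+1))] × Σ(mean rank − 2.5)² = 0.6N × Σ(mean rank − 2.5)².

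With correlation 0.5, the difference between two visits has SD √(2 × (1 − 0.5)) = 1, so a follow-up exceeds baseline with probability Φ(d). For d = 0.3:
- Φ(0.3) = 0.618
- baseline mean rank = 1 + 3 × (1 − 0.618) = 2.146
- each follow-up mean rank = (10 − 2.146)/3 = 2.618
- sum of squares = 0.354² + 3 × 0.118² ≈ 0.167
- N = 80: λ = 0.6 × 80 × 0.167 ≈ 8.0, rejection about 65%
- N = 120: λ ≈ 12.0, rejection about 84%

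**Simulation, same assumptions (pooled Friedman, no IVRS effect).** Repeat runs agree to within about 3 percentage points.

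| Shared shift (SD) | 40 per arm: simulated (analytic) | 60 per arm: simulated (analytic) |
|---|---|---|
| 0.1 | 10% (11%) | 13% (14%) |
| 0.2 | 31% (33%) | 47% (47%) |
| 0.3 | 67% (65%) | 85% (84%) |
| 0.5 | 99% (98%) | >99% (>99%) |

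**Variation: linear shared trend reaching 0.2, 0.3 or 0.5 SD at 6 months, 40 per arm.**

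| Test | 0.2 SD | 0.3 SD | 0.5 SD |
|---|---|---|---|
| Friedman pooled, normal errors | 25% | 50% | 94% |
| Friedman pooled, skewed errors | 76% | 98% | 100% |
| Friedman in the IVRS arm only, normal errors | 13% | 26% | 66% |
| ANOVA time effect, normal errors | 31% | 62% | 98% |

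In the same no-effect settings, the arm-by-visit F test and a Mann-Whitney test on change from baseline reject in about 4% to 6% of trials.

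**Converse: a real difference with no average change** (one arm up 0.25 SD and the other down 0.25 SD by 6 months, a divergence of 0.5 SD). Pooled Friedman rejects in about 4% to 5%. The arm-by-visit F test rejects in 45% to 47% with 40 per arm and 62% to 68% with 60 per arm.

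**The case against.** The strongest reply is that the sentence describes evaluation over time and does not call Friedman the test of the IVRS effect or the only analysis of these scores. This is a condensed article, the hypothesis is plainly between arms, and a fuller plan may name the comparison. The multinomial model could also take the three SF-12 bands in section 3.10 with arm as predictor.

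Part of this stands. A reader might infer that the randomised comparison is excluded; the text leaves it unnamed and does not rule it out. But the objection here is to a test that the document does name for these data and that cannot answer the trial's question. The regression models are assigned no outcome, and logistic models do not suit a score running to 57.

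Other stronger readings also fail:
- That the distribution check changes the question being asked. This presumes that the ANOVA carries an arm term. The text gives it none, so both branches may ask the same time question.
- That any shared change will come out significant. At 0.1 SD the rate is about 10% with 40 per arm.
- That bounded scores must fail a normality check. A maximum alone does not show this, and no score distribution is given.
- That section 4 commits the authors to reporting a time effect as the treatment effect. It is an expectation credited to IVRS, not an analysis rule, and could loosely mean change by arm.

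It is also fair that the main table uses normal data while Friedman is reserved for non-Gaussian data. The skewed runs reject more often, so the direction holds.

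**Conclusion.** The point holds in this form. For two of the three secondary outcomes, the only tests that section 3.12 names for repeated quantitative scores compare visits, and the fallback cannot be extended to compare arms. Followed as written, it can flag an ineffective intervention (about 31% of trials at a shared shift of 0.2 SD and 67% at 0.3 SD with 40 per arm; 47% and 85% with 60 per arm) and miss a real divergence between arms (about 4% to 5% rejection at 0.5 SD).

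These rates rest on the assumed shift, a correlation of 0.5 and pooling of the arms. Friedman within the IVRS arm alone gives lower but still inflated rates. That the Friedman test has no treatment factor depends on none of these assumptions. The outcomes are secondary, and this point makes no claim about the primary adherence analysis. It should be corrected before the data are analysed.

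**What to change.** In section 3.12, state that the effect estimate for K-TUT and SF-12 is a between-arm comparison whatever the distribution. One suitable choice is a single repeated-measures or mixed model with arm, visit and arm-by-visit, taking the arm difference in change from baseline as the effect. If residuals are clearly non-normal, use a between-arm rank test on change, or robust or bootstrap intervals, in place of Friedman. Label any across-visit test as descriptive. In section 4, restate the expected result as a difference between arms in change from baseline.

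The cost is a few sentences, with no new data or patients. The one downside is that a pooled or within-arm change over time no longer counts as evidence that IVRS works.
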